#### Secondary outcome

Furthermore, we assume that adolescents, who show a lack of emotion regulation skills measured with the short form of the *Difficulties in Emotion Regulation Scale* (DERS-SF) [48], will show higher levels of stress, lower QoL, and more mental health problems. The DERS-SF yields a sum score out of 18 items ranging from 0 = *no difficulties at all* to 90 = *extreme lack of regulation strategies*.We assume a correlation between self-perceived stress and self-compassion insofar as the more stress students have, the less self-compassion they show. Therefore, we will measure self-compassion with the German short form of the *Self-Compassion Scale* (SCS-SF) [49].We assume that a lower subjective well-being (WHO-5) [68] will be associated with higher stress levels among adolescents.

The same patterns are expected for psychopathological measurements such as depressive and anxiety symptoms (PHQ-4) [51], eating disorder symptoms (SEED) [54], and poor sleep quality [53, 69]. In order to verify these hypotheses, we will look at the symptom level itself and will also try to create a “psychopathology-score” (PP score) for each participant. This score will be determined by grouping: For every questionnaire, a scale will be drawn up with three different ratings (normal, abnormal, and pathological) by splitting at the 25% and 75% confidence intervals, with normal = 0 points, abnormal = 1 point, and pathological = 2 points. This way an individual score can be calculated for each participant representing his or her psychopathological level of health/illness. Furthermore, we assume the lower the HrQoL, the higher will be the PP score.

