#### Secondary objectives

In addition to the primary outcome, the evaluation of *LessStress* will include the following secondary outcomes: emotion regulation, self-compassion, sleep quality, depression index, anxiety index, self-injurious behaviour, eating disorder symptoms, and health-related quality of life. To investigate adolescents’ resources, we will assess protective and resilience factors (see Table 1 for further details).

**Table 1 Tab1:** Overview of the questionnaires being used

**Instrument**	**Content**	**Length**
**PSS-10:** *Perceived Stress Scale* (primary outcome measure)	Primary objective Developed by Cohen, Kamarck, and Mermelstein, translated and validated by Klein, Brähler et al., 2016 [47]. Investigates the degree to which life was unpredictable, uncontrollable, and overwhelming within the last month. Very good internal consistency (*a* = .84). Positive correlation with depression and anxiety, negative one with quality of life.	10 items
**DERS-SF***: Difficulties in Emotion Regulation Scale Short Form*	Measures emotion (dys-)regulation multidimensional. According to the model by Gratz and Roemer [48], the subscales “non-acceptance”, “problems with target oriented behaviour”, “impulsive conduct problems”, “lack of emotional awareness”, “limited access to emotion regulation strategies”, and “lack of emotional clarity”.	16 items
**SCS:** *Self-Compassion Scale*	The Self-Compassion Scale was developed by Neff in 2003 with 26 items. The shortened version showed satisfactory to good psychometric properties so far [49].	12 items
**WHO-5***: WHO Fragebogen zum Wohlbefinden*	The facets of psychological well-being like mood, interest, energy, and drive within the last 2 weeks are assessed. Used worldwide, non-invasive questions, translated in 30 languages, the first version was published in 1998. Very good internal consistency with *α* = .85. German version by Allgaier [50].	5 items
**PHQ-4***: Gesundheitsfragebogen für Patienten – Depressionsmodul*	The PHQ-4 is a valid screening instrument for symptoms of depression and anxiety symptoms (Cronbach α >0.80) [51]. Responses are scored as 0 (“not at all”), 1 (“several days”), 2 (“more than half the days”), or 3 (“nearly every day”). PHQ–4 scores go from normal (0 –2) to mild (3–5) to moderate (6–8) to severe (9 –12). Symptoms within the last 2 weeks are being interrogated.	4 items

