### Sample size {14}

To analyse cluster-randomised trials, specific constraints must be followed, as individuals within a cluster are assumed to be more similar compared to individuals from different clusters. In order to detect significant effects, the sample size of the trial must be adjusted. This so-called clustering effect (1 + (*m*-1)×*p* [*m* = average number of subjects per cluster; *p* = intraclass correlation coefficient (ICC)]) resulted in an estimated *N* = 1795. For *m*, we assumed an average of 80 within an entire grade as the average class size in Germany varies nationwide (21.2–30.4 students per class), and the ICC was estimated quite conservatively at approximately 0.05 [70] on the basis of the primary outcome. Hence, a clustering effect of 4.95 was determined. Assuming a small effect size (Cohens *d* = 0.2) in universal prevention based on previous studies [71], with a significance level alpha = 0.05 and a power = 0.9, g*power suggests a total of *N* = 306 [72]. Considering the clustering effect, we have to multiply this by 4.95, reaching an overall *N* = 1515. Assuming a dropout rate of 25% due to moving out of the area, sickness, or other reasons, we must add another 379, leading to the final *N* = 1894.

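### The secondary psychopathology score is cut at confidence intervals, which cannot sort individual students; read instead as sample quartiles, its labels are relative to the sample and do not measure illness.

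*Protocol article*

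**What the plan says.** The rule stands in Outcomes {12}, under Secondary outcome: "For every questionnaire, a scale will be drawn up with three different ratings (normal, abnormal, and pathological"), made "by splitting at the 25% and 75% confidence intervals, with normal = 0 points, abnormal = 1 point, and pathological = 2 points". Its purpose follows directly: "This way an individual score can be calculated for each participant representing his or her psychopathological level of health/illness". One hypothesis is tied to the score: "we assume the lower the HrQoL, the higher will be the PP score".

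The section does not say which parameter the intervals belong to, which of their limits is a cut, or which sample supplies them. No other section of the protocol defines the cuts.

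For the PHQ-4, one of the psychopathological measures named in the same section, Table 1 gives severity bands: "PHQ–4 scores go from normal (0 –2) to mild (3–5) to moderate (6–8) to severe (9 –12"). The measures section {18a} repeats the upper three bands. The PP rule makes no use of them.

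**The concern.** The score is meant to say how ill or healthy each student is. That needs cut-points on the scale of individual scores. A confidence interval lies on the scale of an estimate's precision, and its position depends on how many students were recruited. Taken as written, the rule cannot be carried out sensibly.

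The likely intention is the 25th and 75th percentiles of the sample. That can be carried out, but it decides in advance roughly what share of students is called pathological. A reader of the results would take that share as a finding about morbidity when it is a product of the cut. In a universal prevention trial that also plans epidemiological reports from baseline data, this would be misleading.

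**Working it through.** The protocol gives no figure for the PP score, so there is none to reproduce. The check takes the two readings in turn.

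**Inputs.** N = 1515 (Sample size {14}: "reaching an overall *N* = 1515") and N = 1894 ("leading to the final *N* = 1894"). Design effect 4.95, from the same section. It was derived for the primary outcome, so using it for other scales is an assumption. Scores are taken as normal unless stated.

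**Reading 1: confidence intervals of a mean.** Half-width h = z × SD/√N, multiplied by √4.95 = 2.225 to allow for clustering. Share of students inside = 2Φ(h/SD) − 1.

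| Interval | z | N | h (SD) | Share inside | h with design effect | Share inside |
|---|---|---|---|---|---|---|
| 25% | 0.319 | 1515 | 0.008 | 0.7% | 0.018 | 1.5% |
| 75% | 1.150 | 1515 | 0.030 | 2.4% | 0.066 | 5.2% |
| 25% | 0.319 | 1894 | 0.007 | 0.6% | 0.016 | 1.3% |
| 75% | 1.150 | 1894 | 0.026 | 2.1% | 0.059 | 4.7% |

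Example: 1.150/√1515 = 1.150/38.92 = 0.030. Two nested intervals also give four limits where two cuts are needed. A variant takes the 25th and 75th percentile limits of the mean's sampling distribution. Then h = 0.674/38.92 = 0.017 SD, which holds 1.4% of students (0.039 SD and 3.1% with the design effect). Under every variant, nearly everyone falls outside the middle group.

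**Reading 2: sample quartiles, fine-grained scale.** The shares are 25/50/25 by construction, so the mean is 0.25×0 + 0.50×1 + 0.25×2 = 1.0 point. Simulated samples of 1894 with mean severity −1, 0 and +1 SD gave 25.0%, 49.9% and 25.0% each time. A shift of 2 SD in true severity leaves the labels unchanged.

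**Reading 2 on a coarse 0–12 scale.** Assumed negative binomial shapes, capped at 12, at three severity levels:

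| Assumed mean | Sample Q1, Q3 | At or below Q1 | Above Q3 | Score ≥ 6 (moderate or severe band) |
|---|---|---|---|---|
| 1.5 | 0, 2 | 32.8% | 21.3% | 2.7% |
| 3 | 1, 4 | 35.1% | 23.2% | 15.8% |
| 5 | 2, 7 | 32.3% | 22.5% | 36.3% |

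Ties move the shares off 25/50/25. The mean is 1 − (low share) + (high share) = 0.88 to 0.90 points, not 1.0. The pattern persists: the share in the published bands rises from 2.7% to 36.3%, while the share above the sample's upper quartile stays at 21% to 23%. In the first row a student scoring 1 or 2 is rated abnormal by quartiles but lies in the normal band of Table 1.

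**What quartiles still allow.** With cuts pooled over arms and a 0.2 SD difference, solve 0.5Φ(t) + 0.5Φ(t + 0.2) = 0.75. The top category then holds 28.2% of controls and 21.8% of the intervention group. With baseline cuts held fixed, a 0.2 SD improvement moves the share from 25% to 1 − Φ(0.674 + 0.2) = 19.1%.

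**The case against.** The strongest reply is that this is a slip of terminology in a minor outcome. The protocol says that the symptom levels themselves will be examined and presents the score as an attempt in addition. The score is absent from the outcomes listed in Statistical methods {20a}. Its one stated hypothesis is an association with quality of life, which a ranking by quartiles can serve. All of this stands, and it limits the weight of the point. It does not repair the rule, because the quartile reading still fails the purpose that the protocol gives for the score.

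Several stronger conclusions are tempting, and the protocol does not support them:

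- *The score cannot show a programme effect.* The trial compares change between arms, and pooled quartiles keep that contrast. Only a shift common to both arms would vanish, and only if cuts were redone at each wave, which the protocol does not state.
- *Exactly 25% are pathological on every scale, with a mean of exactly 1.0.* This fails on coarse scales because of ties.
- *A literal reading gives 1.4% abnormal and about 49% on each side.* That is one of several literal readings, and it leaves out the design effect.
- *The rule contradicts the PHQ-4 bands.* Table 1 describes the instrument; the PP score is a separate three-level composite. Passing over the bands is a poor choice, not a contradiction.
- *Well-being, self-compassion and resilience would be scored backwards, the self-harm screen would have equal quartiles, and the quality-of-life hypothesis is partly circular through the WHO-5.* These hold only if the rule covers the whole battery. The score is introduced straight after the PHQ-4, SEED and sleep measures, so it may cover only those.

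**Conclusion.** The point holds in limited form. The stated cut rule is wrong as written, so this is not a detail merely left to an analysis plan. Interval limits within about 0.03 SD of the mean (0.07 SD with the design effect) cannot classify students. Read as sample quartiles, the rule labels roughly a quarter of students pathological on a fine-grained scale whatever the morbidity, and 21% to 23% in the coarse-scale examples.

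The conclusion about labels assumes that the quartiles come from the trial's own sample. An external norm sample would not fix the share, but the protocol mentions none. The literal-reading figures assume normal scores, and the 0–12 figures rest on assumed distributions.

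What is lost is the meaning of the labels, not the ability to compare arms or rank students.

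**What to change.** Replace the reference to confidence intervals with stated, fixed cut-offs:

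1. Use published bands where they exist. For the PHQ-4 take the bands in Table 1 and state in advance how four become three, for example normal = 0, mild = 1, moderate or severe = 2.
2. For the other scales use the 25th and 75th percentiles of the pooled baseline sample, held unchanged at T2 and T3, with a rule for ties. Call these categories low, middle and high relative to the sample. They still place about a quarter of students in the top group at baseline, so they must not be called pathological.
3. State that only the symptom scales enter the score. If a scale on which high is good is included, reverse it, and leave the WHO-5 out when the score is related to quality of life.

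Under this scheme 2 points mean a severity band on one scale and a sample rank on another, and the text should say so. A sum of standardised scores would avoid the mixture but gives up the three ratings.

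The cost is a few sentences and a little more scoring code. No data collection changes.

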### Participant timeline {13}

All participants will be assessed using the full battery of instruments as displayed in Table 1. The data assessment will take place 14–30 days after randomisation. For the intervention group (IG), the universal prevention programme *LessStress* will be administered by school staff within the 21 days after baseline. Post-assessment is due within a week after participating the lesson of *LessStress*. Follow-up interviews, using the full battery of questionnaires, will be conducted at 3 months (T2, 104–120 days) and 6 months (T3, 194–210 days) after randomisation. A 14-day window (± 7 days) will be permitted within which to schedule the time points for T2 and 3. For a graphic overview of the study, please see the flowchart in Fig. 2.

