### Who will take informed consent? {26a}

For the trial, the informed consent of the respective schools’ head teachers is required, as well as the informed consent of a legal guardian and of the students. If schools express an interest in participating, a meeting will be organised in order to provide detailed information about the study. In the case of participation, the legal guardians of students in the participating grades/classes will be given detailed written information sheets and will be able to watch an online presentation, in which the study is orally explained. The students will receive posters with information. If students wish to participate, they will provide their written consent by clicking on “Yes, I do want to participate in the study” on the first page of the online survey.

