## Assignment of interventions: allocation

### Sequence generation {16a}

Participating schools will be randomly assigned to one of the two groups using Microsoft Excel. The randomisation will be carried out on the school level following a 1:1 allocation ratio. This enables interference between the IG and WL to be avoided.

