### Concealment mechanism {16b}

The schools will be immediately informed about the allocation via mail. For randomisation, we will use Microsoft Excel. To proceed with organising the appointments and the intervention, schools have to know to which group they have been allocated. The allocation will be executed in the presence of a third independent employee of the clinic (SM).

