### Implementation {16c}

As there are no patients involved in this study, we do not expect a risk of bias associated with the methods of sequence generation and/or inadequate allocation concealment. Schools do have to know in which group they are in, in order to proceed with the organisation of appointments and intervention.

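### Schools learn their arm 14–30 days before students consent and give the baseline PSS-10, so uptake and baseline answers can differ by arm; the reason given for expecting no such bias does not hold

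*Protocol article*

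**What the plan says.** All references are to the protocol article.

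- Unit of allocation, Sequence generation {16a}: "The randomisation will be carried out on the school level following a 1:1 allocation ratio".
- Disclosure, Concealment mechanism {16b}: "The schools will be immediately informed about the allocation via mail".
- Baseline, Participant timeline {13}: "The data assessment will take place 14–30 days after randomisation". This must be the baseline survey, because the following sentence says the lesson "will be administered by school staff within the 21 days after baseline", and T2 and T3 have their own windows.
- Student consent, Who will take informed consent? {26a}: students "provide their written consent by clicking on “Yes, I do want to participate in the study” on the first page of the online survey".
- Guardians, same section: "In the case of participation, the legal guardians of students in the participating grades/classes will be given detailed written information sheets". No date relative to randomisation is given.
- Knowledge of the arm, Procedure for unblinding {17b}: schools and participants know their group. Waiting-list students are told that the lesson comes in 6 months. Students are not told what the study expects to find.
- Expected bias, Implementation {16c}: since the study has no patients, "we do not expect a risk of bias associated with the methods of sequence generation and/or inadequate allocation concealment". Who will be blinded {17a} adds that no ascertainment bias is expected in the questionnaires.
- Comparison, Statistical methods {20a}: the arms are compared on difference in change.

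**The concern.** Randomising schools makes the schools comparable. It makes the students comparable only if the way they enter the study does not depend on the arm. Here each student decides whether to take part after the school has learned its arm. A stressed student may be keener to join when the lesson is weeks away than when it is 6 months away, and staff may promote the survey differently.

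The baseline answers are exposed too. PSS-10 is self-reported in an open trial, so the follow-up scores cannot be shielded from knowledge of the arm. The baseline score can be, and the planned order gives that up. As the comparison is on change, the baseline score enters the effect estimate directly. The target effect is small (d = 0.2 in Sample size {14}), so a modest distortion matters.

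**Working it through.** The plan has no figure of its own to reproduce here. The check has two parts.

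**Order of events.** Counting days from randomisation:

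1. Day 0: the school is allocated and informed ({16a}, {16b}).
2. Days 14–30: students open the survey, consent on its opening page and complete PSS-10 ({13}, {26a}).
3. Up to 21 days after baseline: the lesson, so at the latest day 30 + 21 = 51 ({13}).

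Plans for assessment and collection of outcomes {18a} gives baseline only a season (autumn 2022), which does not contradict this order. No section places student consent or baseline before disclosure, or holds the allocation back from students until baseline is closed. The stated reason for early disclosure ({16b}, {16c}, {17a}) is that schools must organise appointments and the intervention. That supports disclosure before the lesson, not before consent and baseline.

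**Possible size.** The article gives no participation rate and no baseline–follow-up correlation, so all inputs below are assumptions except the yardstick d = 0.2.

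Model: stress Z is standard normal. In one arm P(take part | Z) = 1/(1 + exp(−(a + bZ))), with a set so that overall uptake is p. In the other arm uptake is also p but unrelated to Z. The baseline gap is g = E[Z · P(take part | Z)]/p. With b = 0.3 the odds ratio is exp(0.3) = 1.35 per SD.

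If selection acts on the observed baseline score, and r is the correlation of baseline with follow-up (assumed 0.5 to 0.8), then g·r remains at follow-up and g·(1 − r) appears as a spurious difference in change.

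| Uptake p | Gap g (SD) | In change, g(1 − r) | In an unadjusted follow-up comparison, g·r |
|---|---|---|---|
| 50% | 0.147 | 0.029 to 0.074 | 0.074 to 0.118 |
| 70% | 0.088 | 0.018 to 0.044 | 0.044 to 0.070 |
| 85% | 0.044 | 0.009 to 0.022 | 0.022 to 0.035 |

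Divided by 0.2, the bias in change is about 15–37%, 9–22% and 4–11% of the planned effect. The last column is shown because Outcomes {12} words the primary outcome as group differences at 3 and 6 months, and an unadjusted reading of that would carry more.

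The slope matters as much as the uptake. For b from 0.1 to 0.5 the gap g runs from 0.050 to 0.236 SD at 50% uptake, 0.030 to 0.143 at 70%, and 0.015 to 0.073 at 85%.

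With adjustment for baseline PSS-10, the bias under this model is about zero, because selection acts only on the measured score. The model says nothing about selection on unmeasured factors or about answers altered by knowing the arm.

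**The case against.** The strongest reply is that the exposure is narrower than it looks and partly correctable.

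- The school's signed letter states how many grades and classes take part (Recruitment {15}), apparently before allocation. Students are not told the hypotheses ({17b}), the lesson is given to the class as a whole ({11a}), and every waiting-list school is later offered the programme ({6b}). These points limit the problem. They do not fix which students consent, or what they answer at baseline, before the arm is known.
- Selection on stress is selection on something measured, and baseline adjustment deals with it. This stands. A reader might infer that nothing can be repaired in the analysis, but only selection on unmeasured factors and arm-coloured baseline answers would remain.
- A reader might set the baseline gap directly against d = 0.2 and take the ratio as the bias. The stated comparison is on change, so only g(1 − r) carries over, and at high uptake it is small.
- A reader might infer that parents also decide knowing the arm. Guardian consent is not dated relative to randomisation, so this is not established.
- A reader might count unstratified 1:1 allocation as part of the same fault. Simple randomisation is valid, chance imbalance is not bias, and Study setting {9} says the number of schools cannot be predicted.

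**Conclusion.** The point holds for student consent and the baseline PSS-10: the protocol article places both after the school has been told its arm, and says that participants know their group. The absence of patients is no reason to expect no bias from this order, and {17a} offers no argument for its statement on ascertainment bias.

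The conclusion is that bias can arise, not that it will. Under the assumed slope of 0.3 per SD in one arm only, the baseline gap is about 0.04 to 0.15 SD for uptake of 85% down to 50%, of which a part passes into the difference in change. Near-complete uptake would make the selection component small. The effect on baseline answers of knowing the arm cannot be sized from the document.

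**What to change.** 1. At each school, complete student and guardian consent and the baseline survey, and release that school's allocation only afterwards. Amend {13}, {16b} and {26a} to say so, and date guardian consent.
2. Re-base the windows in {13} that are counted from randomisation. The present T2 and T3 windows are the baseline window plus 90 and 180 days (104 − 14 = 120 − 30 = 90; 194 − 14 = 210 − 30 = 180), so this is largely bookkeeping. Reconcile them with the 21-day limit for the lesson and with {18a}, which starts the intervention directly after baseline and counts follow-up from the intervention.
3. Withdraw the no-bias statements in {16c} and {17a}.
4. Adjust the primary analysis for baseline PSS-10.
5. Report eligible, consenting and baseline-complete numbers by arm and school.

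If baseline cannot be moved at some schools, items 3 to 5 still apply, and baseline scores collected after disclosure should be interpreted with caution.

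Cost: intervention schools have less time between learning their arm and teaching. They now have at least 14 days before baseline, plus up to 21 days after it. If the 21-day limit is kept, they would have at most those 21 days, and the staff training in {11c} must fit within them or be offered to all schools before allocation. No extra students or questionnaires are needed.
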